### Economic evaluation

Economic evaluations will be carried out from a health sector perspective. The components of resource use for the intervention that will be measured will include staff costs and consumables required to deliver the motor training. One-off costs such as equipment and the training materials will be amortised over an assumed life using standard discount rates. Separate evaluations will be conducted for each country using costs in local currencies obtained from study financial statements. As this intervention is being delivered on top of usual care, incremental costs can be estimated without costing usual care provided to all participants.

For those patients discharged during the study, additional health care use in terms of re-hospitalisations will be ascertained from study participants at follow-up in each of the study arms. Costs assigned to such hospitalisations recorded during follow-up will be based on published cost weights (for example, in Australia these will be sourced from the Independent Hospital Pricing Authority [52]).

At 6 months, health utilities derived from EQ-5D-5L scores (based on a relevant value set) will be multiplied by survival up to 6 months (although we expect deaths before 6 months to be very low). This will enable an estimate of QALY gain over 6 months for each participant, and in turn an estimate of the difference in average quality-adjusted life years between Motor Training and Usual Care Groups. The overall effectiveness of the intervention across the study will be used in each of the cost-effectiveness estimates. Set alongside country-specific incremental costs, an estimate of the incremental cost-effectiveness ratio will be derived for each country. Usual one way and probabilistic sensitivity analyses will be conducted to take into account uncertainty in estimates. The incremental cost-effectiveness ratio will be benchmarked against prevailing cost-effectiveness thresholds.

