### Interventions

#### Usual care

In keeping with the pragmatic orientation of the trial, both groups will receive the physiotherapy and occupational therapy typically provided to inpatients at the site [24]. It is anticipated that for most sites this will be 3 to 6 sessions per week of both occupational therapy and physiotherapy. Some sites may also provide group classes, hydrotherapy and sessions with exercise physiologists. At some sites, usual care could include some components of the motor training intervention.

The amount and type of usual care at each site will be recorded. Specifically, the following variables will be collected: the date, time and length of both scheduled and delivered physiotherapy and occupational therapy sessions. We will differentiate scheduled and delivered sessions because scheduled sessions are often missed due to illness, medical appointments and other reasons. In addition, the time spent on seven broad types of commonly administered therapies [34] will be collected using the International SCI Physical Therapy-Occupational Therapy Basic Data Set [4].

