#### Secondary outcomes

The effect of the intervention on upper and lower limb strength, sensation, independence, ability to walk, quality of life, perceptions of the ability to perform self-selected goals, and impressions of therapeutic benefit will be estimated using the same statistical model used in the primary analysis. For outcomes measured at both 10 weeks and 6 months, both visits will be included in the model and correlations between repeated measures will be modelled by including a random patient intercept and the effect of the intervention will be estimated at each visit by a fixed term for visit together with its interaction with the intervention.

Similar models will be used to estimate the effect of the intervention on participants’ impressions of therapeutic benefit. However, as baseline values are not collected for this outcome variable, baseline Total Motor Score will be used in the model as a pre-randomisation covariate.

The effect of the intervention on time to discharge will be estimated from a Cox model that includes baseline Total Motor Score and the stratification variables (severity as a fixed effect and site as a random effect). Patients will be censored at 6 months or when they were last known to be in hospital, whichever occurs earlier.

The effect of the intervention on type of SCI (AIS grade—5 levels) will be estimated using an ordinal logistic regression model that includes baseline AIS grade and the stratification variables. The effect of the the intervention will be estimated as the odds ratio corresponding to the odds of shifting to a worse grade category.

No subgroup, adjusted or imputed analyses are planned for any of the secondary outcomes.

If there is more than 20% non-adherence (defined as less than 80 h of additional motor training), methods of causal inference will be used to estimate the effects of intervention in the principal stratum of people who would comply with both assigned and (counterfactual) unassigned interventions [49]. Modern methods of causal mediation analysis will also be used to determine the extent to which the effects of the intervention are mediated by time spent in training [50, 51].

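### The incremental cost rule is valid only if inpatient resource use is equal by arm, yet the index stay is in neither cost component and time to discharge is a trial outcome

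*Protocol article*

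**What the plan says.** All references are to the protocol article.

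- **Perspective** (Economic evaluation): "Economic evaluations will be carried out from a health sector perspective".
- **Intervention cost** (same section): the measured components "will include staff costs and consumables required to deliver the motor training", with one-off equipment and training materials amortised.
- **Usual care** (same section): because training is added to usual care, "incremental costs can be estimated without costing usual care provided to all participants".
- **Hospital use** (same section): "For those patients discharged during the study, additional health care use in terms of re-hospitalisations will be ascertained", with published cost weights applied to those admissions. No other hospital use is named.
- **Length of stay**: the Introduction lists it among the secondary aims, and time to discharge is one of the 11 secondary outcomes. Under Secondary outcomes, "The effect of the intervention on time to discharge will be estimated from a Cox model", with censoring at 6 months or when the participant was last known to be in hospital, if earlier.
- **Usual therapy**: the Usual care section records "the date, time and length of both scheduled and delivered physiotherapy and occupational therapy sessions".

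**The concern.** A cost drops out of an incremental comparison only when both arms consume the same amount of it. That training is delivered on top of usual care describes what each arm is offered. It does not establish that the arms use the same quantity of inpatient care, and the trial sets out to estimate whether they differ in length of stay.

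The costing as described is also uneven. A hospital day counts if the participant has gone home and been readmitted, but nothing in the section counts it if the participant never left. An arm discharged earlier gets no credit for the days saved, yet has more time at risk of a costed readmission. An arm kept longer carries no counted cost for the extra days.

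The report could therefore show an effect on discharge beside country-specific cost-effectiveness ratios that ignore it. The Discussion says rollout will depend on cost and gives this as a reason for the economic analysis. The planned one-way and probabilistic sensitivity analyses cannot repair this, because they vary components that are in the model and cannot recover one that was never entered.

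**Working it through.** The article states no economic figure, so there is nothing to reproduce. What can be checked is how large a difference in stay would have to be to matter.

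**Inputs**

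- Planned training: 12 h per week for 10 weeks (Motor training), so 12 × 10 = 120 h per participant.
- Usual therapy: a median of 3.8 to 5 h per week in the observational work cited in the Introduction, so 38 to 50 h over 10 weeks.
- Cost of one bed-day relative to one training hour, *r*: not in the article. Assumed range 5 to 30.
- Difference in mean index days, training minus usual care, *d*: unknown in size and sign.

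**Formulas**, in units of the cost of one training hour and leaving re-hospitalisations aside:

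- Incremental cost without the index stay = 120.
- Incremental cost with the index stay = 120 + *r* × *d*.
- Difference in stay that equals the whole training cost = 120 / *r*.
- Shift from a 7-day difference, as a share of training cost = 7*r* / 120.

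**Results**

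| *r* (assumed) | 120 / *r* (days) | 7*r* / 120 | Cost if stay is 7 days shorter | Cost if stay is 7 days longer |
|---|---|---|---|---|
| 5 | 24 | 35/120 = 29% | 85 | 155 |
| 10 | 12 | 70/120 = 58% | 50 | 190 |
| 20 | 6 | 140/120 = 117% | −20 | 260 |
| 30 | 4 | 210/120 = 175% | −90 | 330 |

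At *r* = 20 or 30, a stay one week shorter turns a counted cost of 120 into a saving. At *r* = 5 or 10 the sign holds, but the amount still moves by 29% or 58%.

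**Displaced usual therapy.** If 10% of usual therapy were displaced (an assumption), the offset would be 0.10 × 38 to 50 h = 3.8 to 5 h, or about 3% to 4% of 120 h. This term is minor beside the index stay.

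**Is there room for stays to differ?** Participants must be likely to remain inpatients for 10 weeks, so most divergence would come later. Discharge is followed to 6 months, about 26 weeks, which leaves about 26 − 10 = 16 weeks.

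**The case against.** The strongest reply is that the article never says the index stay is excluded. The sentence about usual care can be read with the Usual care section, which describes physiotherapy, occupational therapy and related sessions, not bed-days. The list of intervention costs need not be exhaustive, and a condensed article may leave further cost items to the full protocol. On that reading, the only stated exclusion is usual therapy, where the effect is small.

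Part of this stands. A reader might infer that the plan explicitly removes the index stay; it does not. The omission follows by implication, because the stay is part of inpatient usual care and is named in neither component. But the point does not rest on silence alone. The section gives a reason for not costing usual care, and that reason needs equal consumption by arm. It also specifies which hospital use will be costed, and that use begins after discharge. Followed as written, the plan could give a biased incremental cost.

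A reader might also infer that training will crowd out usual sessions, since the article says scheduled sessions are often missed. It attributes this to illness, medical appointments and other reasons, and does not mention competing training. Both groups are to continue usual care. Displacement is possible but not indicated.

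Finally, the size rests wholly on an assumed cost ratio. That is correct, and it is why only a range is given.

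**Conclusion.** The point holds in a conditional form. The cost rule is valid only if inpatient resource use is equal by arm, and the trial's own secondary aim leaves that open for length of stay. If index stays differ, each country's incremental cost and ratio will be biased by the difference times the bed-day cost.

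Under the assumed range of 5 to 30 training hours per bed-day, a difference of 24 to 4 days equals the whole planned training cost, and a 7-day difference shifts incremental cost by 29% to 175% of it. If stay and usual therapy prove equal, the omission does no harm.

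It is tempting to conclude that the ratios will be badly wrong or have the wrong sign. The article does not support that: it gives no unit costs and no expected size or direction for the difference in stay. A change of sign needs a shorter stay in the training arm that exceeds the break-even value. The primary outcome and its analysis are unaffected.

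**What to change.** Replace the sentence on usual care with text to this effect: *Incremental cost will include index-admission bed-days from randomisation to discharge or 6 months, by arm, at a country-specific unit cost, in addition to training costs and re-hospitalisations. Delivered usual physiotherapy and occupational therapy will be costed separately only where the bed-day cost excludes therapy.* The second sentence prevents therapy being counted twice.

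Keep the figure based on training plus re-hospitalisation as a sensitivity analysis, so that readers can see how much the index stay contributes. The costing needs the difference in mean bed-days to 6 months, since a hazard ratio from the Cox model cannot be multiplied by a unit cost. A rule will be needed for participants last known to be in hospital before 6 months.

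The change costs little. Time to discharge is already collected to 6 months, so the additions are one bed-day unit cost per country and some analysis work. Where therapy has to be costed separately, a therapy unit cost is needed too, along with a check that the session records cover the costed period. The downside is a wider interval for incremental cost.

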#### Motor training

Participants allocated to the Motor Training Group will receive, in addition to usual care, an extra 12 h of motor training each week for 10 weeks. This will commence within two business days of randomisation. The 12 h per week of motor training can be provided at any time although it is anticipated that most sites will administer the additional motor training over five 2-h sessions on each weekday of the week. Some sites may provide the training in longer sessions on Saturdays and Sundays, or both. The therapy involves active, targeted motor training of neurologically-weak muscles below the level of the injury, and may consist of practice of functional activities using the principles of task-specific training, or isolated muscle contractions directed at improving strength or motor control. For example, a participant with some motor activity in the lower limbs will receive intensive task-specific training focusing on regaining the ability to sit, stand and walk. This could involve task-specific training of sitting, standing, gait training on a treadmill with bodyweight support or the use of robotic gait devices. A participant with some motor activity in the upper limbs and hands will receive intensive training of a range of reaching and grasping tasks. Training will be supplemented, where available and at the therapist’s discretion, with biofeedback, electrical stimulation, mental imagery and somatosensory stimulation. Robotics and computer game-based therapy will be used where available and appropriate provided they encourage active contraction of neurologically-weak muscles. Importantly, treatments will be individualised to the needs of each participant and follow key principles of task-specific training and strength training as outlined in a detailed intervention manual compiled for the trial. All training will address a participant’s specific motor problems. Details of the motor training provided to participants will be recorded with the same forms used to document usual care.

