### Outcome measures

Outcome data will be collected at baseline (prior to randomisation), and then 10 weeks (±2 weeks) and 6 months (±4 weeks) after randomisation by independent blinded assessors. The baseline and 10-week assessments will be conducted face-to-face and the 6-month assessments will be conducted by telephone. For this reason, motor and sensory scores and AIS grades will not be collected at 6 months. The success of assessor blinding will be monitored and reported.

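### QALYs are written as the 6-month EQ-5D-5L utility times survival, which credits that utility to the whole half-year although two earlier measurements are scheduled

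*Protocol article*

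**What the plan says.** The Economic evaluation section of the protocol article sets out the calculation in one sentence: "At 6 months, health utilities derived from EQ-5D-5L scores (based on a relevant value set) will be multiplied by survival up to 6 months". A parenthesis adds "although we expect deaths before 6 months to be very low". The result is then put to use: "This will enable an estimate of QALY gain over 6 months for each participant", and from there "an estimate of the difference in average quality-adjusted life years between Motor Training and Usual Care Groups". That difference is the effect side of the ratio: "Set alongside country-specific incremental costs, an estimate of the incremental cost-effectiveness ratio will be derived for each country".

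Two other sections bear on this. Outcome measures gives the visit times: "Outcome data will be collected at baseline (prior to randomisation), and then 10 weeks (±2 weeks) and 6 months (±4 weeks) after randomisation". The EQ-5D-5L row of Table 2 is ticked at all three visits. Under Motor training, the intervention is "an extra 12 h of motor training each week for 10 weeks", so it ends at about the second visit.

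**The concern.** A QALY is utility accumulated over time. One utility value multiplied by duration gives the right total only if utility stayed at that value throughout. That is implausible here. Participants enter within 10 weeks of a spinal cord injury and are expected to recover, and a treatment that has not started cannot have changed utility at randomisation. Because few deaths are expected, survival is close to 0.5 year for nearly everyone, so the rule reduces to about half of the 6-month utility. The 10-week value, taken as training ends, has no role in the rule as written.

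At stake is the denominator of every country's cost-effectiveness ratio, which is to be compared with the prevailing thresholds. The Discussion names cost as one of the things on which any rollout will depend. The one-way and probabilistic sensitivity analyses that are planned are not described as varying the way QALYs are built.

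**Working it through.** The document states no QALY or cost-effectiveness figure, so there is nothing to reproduce. The check compares the written rule with the area under the utility curve through the three scheduled visits.

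**Inputs from the document**
- Visits at 0, 10 weeks (10/52 = 0.1923 year) and 6 months (0.5 year).
- Deaths very few, so survival is taken as 0.5 year.

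**Assumptions (not in the document)**
- d0, d10 and d26 are the between-group utility differences at baseline, 10 weeks and 6 months.
- d0 = 0, the expected value under randomisation.
- d26 = 0.05 for illustration. The factors below depend only on d10/d26, not on this value.

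**Formulas**
- Written rule: 0.5 × d26.
- Area under the curve: (10/52)(d0 + d10)/2 + (0.5 − 10/52)(d10 + d26)/2 = 0.0962 d0 + 0.25 d10 + 0.1538 d26.
- Factor with d0 = 0: 0.5 / (0.25 × d10/d26 + 0.1538).

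**Results**

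| Assumed path of the effect | d10 | d26 | Written rule | Area under curve | Factor on QALY difference | Factor on cost-effectiveness ratio |
|---|---|---|---|---|---|---|
| Complete by 10 weeks, held | 0.05 | 0.05 | 0.0250 | 0.0202 | 1.24 | 0.81 |
| Half present at 10 weeks | 0.025 | 0.05 | 0.0250 | 0.0139 | 1.79 | 0.56 |
| Linear growth | 0.0192 | 0.05 | 0.0250 | 0.0125 | 2.00 | 0.50 |
| Only after 10 weeks | 0 | 0.05 | 0.0250 | 0.0077 | 3.25 | 0.31 |
| 10-week effect twice the 6-month effect | 0.10 | 0.05 | 0.0250 | 0.0327 | 0.76 | 1.31 |
| Present at 10 weeks, gone by 6 months | 0.05 | 0 | 0 | 0.0125 | 0 | undefined |

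**Turning points**
- The two methods agree when 0.25 × d10/d26 + 0.1538 = 0.5, that is d10/d26 = 1.38. Above this the written rule understates the QALY difference.
- The factor reaches 2 when 0.25 × d10/d26 + 0.1538 = 0.25, that is d10/d26 = 0.38. A factor of two or more therefore needs a 10-week effect of at most 38% of the 6-month effect.

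**The case against.** The strongest reply is about reading. The phrase on 6 months that opens the sentence can mark when the calculation is done, with utilities from the whole period weighted by time alive. An individual gain suggests a reference value such as baseline, and a schedule with the EQ-5D-5L at three visits suggests that a path over time was intended. This reply has some force: the document never says that the earlier utilities will be discarded, and a reader should not take that as the stated intention. But the sentence names one time and one multiplication, and an analyst who followed it literally would get the wrong quantity. It needs rewording on either reading.

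The second reply is that this is a condensed article, and that integration rules, handling of death and baseline adjustment belong in the full protocol or an economic plan. That is right for those details, and their absence is not the point here. The multiplication, however, is stated.

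A reader might also infer that the result will be wrong by a factor of two. The document does not support this. All training is given in the first 10 weeks, and the path in which the effect is complete by then and held gives 1.24.

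Nor does a chance imbalance in baseline utility pass directly into the QALY difference under the written rule. Baseline does not enter that formula and acts only through its correlation with the 6-month value. It enters directly, with weight 0.0962, once an area under the curve is used, which is why the fix includes adjustment for it.

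**Conclusion.** The point holds for the sentence as written. The 6-month utility times survival does not measure QALYs over 6 months in people whose utility is changing, and the measurements for a proper calculation are already scheduled.

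For effects that hold or grow after 10 weeks, the rule overstates the QALY difference by 1.24 to 3.25 times and makes the intervention look more cost-effective than it is. For effects that fade enough, it errs the other way, and if nothing remains at 6 months it gives no gain and no defined ratio. These figures assume no baseline difference, survival of 0.5 year, and straight lines between visits. Which path applies, and so even the direction of the error, cannot be known from the document.

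The sentence should be corrected before the economic analysis. The primary outcome, sample size, interim analysis and clinical conclusions are untouched.

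**What to change.** Replace the sentence in Economic evaluation with wording such as: *QALYs to 6 months will be calculated for each participant as the area under the EQ-5D-5L utility curve (trapezoidal rule) through baseline, 10 weeks and 6 months, with utility zero from death. The between-group difference will be estimated by regression adjusting for baseline utility and the stratification variables. Missing utilities will be handled by multiple imputation.*

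The cost is a change of wording; no new data are needed. There is one small downside: a participant who misses any of the three visits has no QALY unless a missing-data rule is given. Multiple imputation is one example of such a rule. If the sponsor already intended to use all three visits, the same text simply makes that explicit.

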### Data integrity

Baseline and 10-week assessment data will be collected in paper format and transferred to George Clinical for double data entry into a REDCap database. There will be automatic checks for errors and data queries will be emailed to the sites and stored on the database. Electronically transcribed data will be managed by the Biostatistics and Data Management Division of George Clinical.

